#### 2.4.3. Inclusion Criteria

Participants should be between 18 and 70 years of ageParticipants should meet the diagnostic criteria for IGTAfter a month of routine diet and exercise intervention, participants should meet the diagnostic criteria for IGTOverweight or obesity, body mass index (BMI) ≥  24 kg/m^2^According to syndrome pattern differentiation referred to the Diabetes Evidence-based Clinical Practice Guideline in TCM and guidelines delineated in the Clinical Research of New Investigational Drugs in Traditional Chinese MedicineParticipants should sign informed consent forms

#### 2.4.4. Exclusion Criteria

Participants who had acute cardiovascular events, myocardial infarction, or stroke within the past 6 monthsParticipants with serum transaminase level two times higher than the upper limit of normal value and serum creatinine two times higher than the upper limit of normal valueParticipants whose blood glucose rise is caused by a stress state or secondary reasonParticipants with psychiatric conditionsPregnant, lactating women, or having a history of drug allergyParticipants with severe cardiovascular and respiratory disease or severe complications of the liver, kidney, brain, or other primary diseasesParticipants who suffered acute infections and severe infectionsParticipants who have used hypoglycemic drugs in the past 3 months

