## 2. Methods

### 2.1. Trial Design

This study is a multicenter cohort study with two arms. A total of 600 participants will be recruited. The participants will be divided into either intervention or control groups according to their own desire, and the exposure factor is the application of TCPMs. All participants will be encouraged to lead a healthy lifestyle, and the intervention group also used TCPMs based on syndrome differentiation. Incident diabetes and normalization of blood glucose are indexes of end point. Safety assessments and adverse event monitoring will also be conducted. The treatment duration is set for 24 weeks, and we will follow-up for another 2 years.

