### 2.3. Study Population and Recruitment

A total of 600 participants will be recruited from six hospitals in mainland China, including Guang'anmen Hospital of the China Academy of Chinese Medical Sciences, Beijing Shijitan Hospital, Capital Medical University, Beijing Changping District Hospital of Chinese Medicine, Beijing Shunyi District Hospital of Chinese Medicine, Beijing Miyun District Hospital of Chinese Medicine, and Beijing Pinggu District Hospital of Chinese Medicine. The participants will be divided into either the intervention group or the control group (1 : 1). Participants should be included according to the diagnostic criteria and inclusion criteria and should be refused according to the exclusion criteria. Eligibility criteria are listed as follows.

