### 2.5. Interventions

The participants will be divided into either the intervention group or the control group (1 : 1). The control groups will conduct lifestyle intervention alone, and the intervention group will use TCPMs on the basis of lifestyle intervention.

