#### 2.6.4. Safety Assessment

Vital signs (body temperature, blood pressure, respiration, and heart rate), electrocardiogram (ECG), routine blood test, routine urine test, and routine stool test are evaluated at baseline and week 24Liver function including alanine aminotransferase (ALT) and aspartate aminotransferase (AST) and renal function, including serum creatinine (SCr) and blood urea nitrogen (BUN), at baseline and week 24

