## Figures and Tables

**Figure 1 fig1:**
[figure not shown]
Flow diagram of enrollment, intervention, and assessments.

**Table 1 tab1:** Schedule of enrollment, allocation, visits, and assessments.

Time of visits	Enrolment	Allocation	Drug intervention period				Follow-up period			
	−2w	0w	4w, 8w	12w	16w, 20w	24w	12 m	18 m	24 m	30 m
*Collect basic medical history*										
Sign informed consent form	√									
Determine inclusion and exclusion criteria	√	√								
Determine withdrawal criteria	√	√	√	√	√	√	√	√	√	√
Fill in general information	√	√								
History of prediabetes and treatment	√									
Comorbidity and symptom	√									
Physical examination and consultation	√	√	√	√	√	√	√	√	√	√
Concomitant medication	√	√	√	√	√	√	√	√	√	√

*Efficacy assessment*										
Glycosylated hemoglobin		√		√		√	√	√	√	√
Fasting plasma glucose		√	√	√	√	√	√	√	√	√
2-hour postprandial blood glucose		√	√	√	√	√	√	√	√	√
Blood lipids		√		√		√	√	√	√	√
Carotic artery intima-media thickness		√		√		√	√	√	√	√
BMI, waist perimeter and hip perimeter, waist-hip ratio, and blood pressure		√	√	√	√	√	√	√	√	√
TCM symptom score		√		√		√	√	√	√	√

*Safety assessment*										
Vital signs		√				√	√	√	√	√
Routine blood, urine, and stool examination		√				√	√	√	√	√
Liver function		√				√	√	√	√	√
Renal function		√				√	√	√	√	√
Electrocardiogram		√				√	√	√	√	√
Hypoglycemic episodes			√	√	√	√	√	√	√	√
Adverse events			√	√	√	√	√	√	√	√

*Other work*										
Record of TCPMs		√	√	√	√	√	√	√	√	√
Research summary						√				√

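### The liver and kidney laboratory exclusion joins its two limits with *and*, so read literally a single raised value does not exclude, and the six sites could apply it differently

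*Protocol article*

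**What the plan says.** Section 2.4.4 contains one laboratory criterion for liver and kidney together: "serum transaminase level two times higher than the upper limit of normal value and serum creatinine two times higher than the upper limit" of normal. Section 2.3 makes the list operative: people "should be refused according to the exclusion criteria".

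The same list has one other item that touches these organs. It covers severe complications of the liver, kidney and other organs and gives no laboratory limit. The inclusion criteria in 2.4.3 set no liver or kidney limit.

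On exposure, 2.1 states "The treatment duration is set for 24 weeks", and 2.5 states that "the intervention group will use TCPMs on the basis of lifestyle intervention"; the control group has lifestyle intervention alone. On testing, 2.6.4 schedules liver function and "renal function, including serum creatinine (SCr) and blood urea nitrogen (BUN), at baseline and week 24". In Table 1 the row "Liver function" and the renal row are ticked at week 0 and week 24, with nothing between, and then at the follow-up visits.

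**The concern.** An exclusion that requires two abnormalities at once is much narrower than two exclusions that each require one. If a site follows the line as printed, a participant with an isolated raised transaminase, or an isolated raised creatinine, passes the laboratory screen. If another site takes the line as two limits listed together, it refuses the same person. Six hospitals recruit, so the enrolled population could differ by site for a reason unrelated to the study question.

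Two things are at stake. The first is participant protection, which is the evident purpose of the criterion. The second is the clarity of the safety comparison: ALT, AST, creatinine and urea nitrogen are the named liver and renal safety tests. Participants choose their own group, so randomisation does not balance abnormalities present at entry.

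**Working it through.** The plan states no figure on this point, so there is nothing to reproduce. The check is one of logic, followed by an illustration of size.

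**Step 1. The criterion under each reading.** Limits are those in 2.4.4 (above twice the upper limit of normal).

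| Transaminase raised | Creatinine raised | Excluded if both are required (literal) | Excluded if either suffices |
|---|---|---|---|
| no | no | no | no |
| yes | no | no | yes |
| no | yes | no | yes |
| yes | yes | yes | yes |

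The literal reading excludes 1 of 4 combinations and the alternative 3 of 4. The readings part on exactly the two isolated abnormalities.

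**Step 2. Does anything else refuse those two groups?**

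- Inclusion criteria (2.4.3): no liver or kidney limit.
- Severe liver or kidney complications (2.4.4): may catch some of these people, when the investigator judges the disease severe. It does not reach an isolated laboratory rise without severe disease.
- Suspension criteria (2.4.5): abnormal results count when clearly related to the study drug, so a rise already present at entry is not covered.
- Scheduled testing (2.6.4, Table 1): week 0 and week 24 in the drug period, so no planned test would bring the matter up in between.

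**Step 3. Illustration of size.** The documents give no prevalences. Assume that a proportion *a* of those screened exceed the transaminase limit and a proportion *c* the creatinine limit, independently. Per 600 screened:

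- refused if both are required = 600 × a × c
- refused if either suffices = 600 × (a + c − a × c)

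| a | c | Both required | Either suffices |
|---|---|---|---|
| 2% | 0.5% | 600 × 0.0001 = 0.06 | 600 × 0.0249 = 14.9 |
| 5% | 1% | 600 × 0.0005 = 0.3 | 600 × 0.0595 = 35.7 |
| 10% | 1% | 600 × 0.001 = 0.6 | 600 × 0.109 = 65.4 |

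Positive correlation narrows the gap. In the extreme case where everyone with raised creatinine also has raised transaminase, the middle row becomes 600 × 0.01 = 6 against 600 × 0.05 = 30. The readings still differ for 24 people.

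**The case against.** The best defence is that every site will understand what was meant. The same list uses *and* loosely elsewhere, for example when it pairs acute with severe infection, and the criterion states its threshold separately for each test, which fits two limits set side by side. This has force: the authors may well have meant each limit to exclude alone. But the document's style does not settle the matter. The same list uses *or* for alternatives in other items, and impaired glucose tolerance is described with *and* in the Background but defined with *or* in 2.4.1. What stands is that this is a wording defect open to different application.

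Three stronger readings are tempting, and the documents do not support them.

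- A reader might infer that sites are obliged to enrol people with one raised value. The line is ambiguous, and the severe-disease exclusion allows some of them to be refused.
- A reader might infer from Table 1 that eligibility is settled before liver and renal results exist, because these tests are not scheduled at week −2. The table ticks the eligibility check at week 0 as well, the visit at which the tests are scheduled, and it does not give the order of events within that visit.
- A reader might infer that a high week-24 value in someone abnormal at entry says nothing about the drug. A baseline value exists, so change can be calculated; the control group has the same schedule; and the causality assessment in 2.8 considers the patient's clinical condition. Interpretation is harder, not impossible.

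**Conclusion.** The concern holds as a defect in an operative eligibility rule. Followed as printed, 2.4.4 does not refuse a person with only one of the two values above its limit, and no other provision reliably does. The exposure to study drug applies only to those who choose the intervention group.

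The logical result (1 of 4 combinations excluded against 3 of 4) rests on the text alone. The counts per 600 screened are only an illustration: they depend on prevalences and independence that the documents do not supply, and on every site taking the literal reading. The qualitative conclusion needs only that isolated elevations are commoner than joint ones.

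The point touches no primary outcome, sample size or planned test, so it ranks as a clarification worth making for participant protection and consistency between sites, below faults that threaten the main analysis. Which clinical limit is appropriate is not judged here.

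**What to change.** Reword 2.4.4 so that the two limits already in the protocol appear as separate exclusion criteria, each sufficient alone. If the sponsor does intend them to apply only jointly, the text should say so explicitly. In either case, reconcile the line with the exclusion for severe liver or kidney complications, so that all six hospitals know how the two relate. Table 1 needs no change for this point.

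The cost is one line of wording and notice to the sites. No test is added. If the limits are separated, a few more people will fail screening.

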#### 2.4.5. Suspension Criteria

Participants who experience severe disease or physiological changes, who are not suitable for further studyParticipants whose blood glucose increased obviously or having severe or frequent hypoglycemia should be withdrawn from the study, and the effect will be judged as invalid, which is a complete caseAn allergic reaction that is clearly associated with the study drugAdverse symptoms or signs and abnormal examination results occur that are clearly related to intake of the study drugParticipants who show poor drug compliance, such as failure to take at least 80% and no more than 120% of the prescribed amount of medicineWomen who develop pregnancy during the studyParticipants who are reluctant to continue this studyNational laws, ministry of science and technology, or other authorities decide to terminate the study

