### 2.4. Eligibility Criteria

#### 2.4.1. Diagnostic Criteria

Impaired glucose tolerance (IGT) is defined according to the 1999 WHO criteria: FBG <7.0 mmol/L or 2h PBG ≥7.8 and <11.1 mmol/L.

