### 2.6. Outcome Measurement

#### 2.6.1. Indexes of End Point

Incident diabetes according to the guideline for the prevention and treatment of type 2 diabetes (2017 edition)Normalization of Blood Glucose, FPG <5.6 mmol/L or 2h PBG <7.8 mmol/L

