### 2.8. Adverse Event Monitoring

Any adverse events (AEs), such as subjective discomfort of participants and abnormal laboratory tests, should be treated seriously, analyzed carefully, and addressed immediately. An adverse event report form will be recorded at every visit, including the occurrence time, severity, duration, adopted measure, and transfer. Every AE will be classified as a mild, moderate, or severe AE, and its relationship between AEs and the intervention drugs will be judged: whether the reasonable relationship exists between the time of drug use and the occurrence of suspicious AEs; whether the suspected AEs conform to the known adverse reactions of the drug; whether the suspicious AEs can be explained by the effect of combined drugs, the clinical condition of patients, or the effect of other therapies; whether the suspected AEs will disappear or alleviate after drug withdrawal or dosage reduction; and whether the same AEs will occur again after reexposure to intervention drugs. Severe AEs will be reported to the principal investigator and the Ethics Committee immediately, and the “Severe Adverse Event (SAE)” form is filled out. The severe adverse events should also be reported to the safety supervision division of the State Food and Drug Administration within 24 hours. All AEs must be treated until properly resolved, retested in 24 hours, 7 days, and 14 days according to the situation, informed the clinical supervisor of the results, and tracked until they are stable.

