### 2.10. Sample Size Calculation

According to previously published research [11], the annual conversion rate of IGT into T2DM was 1.5% in the TCM group and 10% in the control group. We predicted that the annual conversion rate of IGT into T2DM was 5.7% in the TCM comprehensive intervention group. Therefore, assuming that *α* = 0.05 and *β* = 0.1 according to the one-sided test, u*α* = 1.645 and u*β* = 1.282, and the data will be placed in the formula to obtain *n* = 299.94. Therefore, each group needs more than 300 participants, for a total of 600 participants.

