### 2.11. Statistical Analysis

Three datasets will be used for statistical analysis, including a full-analysis set (FAS), per-protocol analysis set (PPS), and safety analysis set (SS). The FAS is the dataset composed of participants who have at least one postmedication evaluation data. The last observation carried forward (LOCF) method will be used for the missing data supplement. The PPS is the dataset composed of participants who meet the inclusion criteria, show good compliance, and complete the treatment plan. The SS is the dataset of all participants randomized to study, and safety record will be assessed, including adverse events and laboratory test results. All statistical tests are two-sided tests, and *P* < 0.05 will be considered statistically significant. Enumeration data will be expressed as frequency and analyzed using the chi-square test or Wilcoxon rank sum test. Measurement data will be described by means, standard deviation, maximum value, and minimum value and compared between groups using the group *t*-test, Fisher's exact test, or Wilcoxon rank sum test. Statistical analysis will be completed by the third-party statisticians.

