## 3. Discussion

In the present clinical practice in China, prevention of T2DM mainly depends on the improvements in unhealthy lifestyles, which is hard to persist in. Several large-scale trials have demonstrated that use of some hypoglycemic drugs can decrease the incidence of diabetes to various degrees in those with prediabetes [12–15], though none are approved by the U.S. Food and Drug Administration, specifically for diabetes prevention. The cost, adverse reactions, tolerance, and other factors are also needed to be considered [4, 16]. TCM may hold a promise in the prevention of T2DM because of its characteristics of “treat disease before it arises,” which include strengthening the body constitution and regulating the high-risk factors leading to diabetes; in addition, TCM could also control the development of T2DM. This cognition corresponds with the thought of the prevention of T2DM. Prediabetes may fall under the TCM patterns of “spleen pyretic abundance,” etc. [17]. The main pathogenesis lies in spleen and stomach congestion, dampness-heat accumulation in the spleen, spleen deficiency and phlegm obstruction, liver depression and qi stagnation, and qi-yin dual insufficiency [9, 10]. In China, many prediabetic patients are more likely to choose the complementary TCPMs. Postmarketing TCPMs possess steady drug composition and defined dosage, which is convenient to observe the efficacy. In recent years, some randomized controlled trials (RCTs) have proved that TCPMs alone or TCPMs combined with lifestyle modification could be an effective intervention for the preventative treatment of T2DM [18–20]. Now, we aim to implement a clinical trial to observe the efficacy of TCPMs in the prevention of T2DM in Chinese subjects. The strength of our trial is that the trial design is a prospective cohort study, not an RCT, and the choice of intervention drugs in our trials is based on syndrome differentiation and treatment, which are more in accord with the clinical practice of TCM. The treatment duration is 6 months, and follow-up is continued for another two years, which is to observe the short-term and long-term effects of TCPMs. As to outcome assessment, we emphasize for incident diabetes and normalization of blood glucose, improvement of symptoms is also important for prediabetic patients to increase the quality of life.

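### A marked glucose rise takes the participant out of the study, so follow-up for incident diabetes stops on a sign of that end point

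*Protocol article*

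**What the plan says.** Section 2.4.5 (Suspension Criteria) directs that participants whose "blood glucose increased obviously or having severe or frequent hypoglycemia should be withdrawn from the study, and the effect will be judged as invalid"; the sentence then describes this as a complete case. No glucose threshold or confirmatory test is attached, and the exit is from the study, not only from the drug.

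Other parts of the protocol article that bear on this:

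- **Entry (2.4.1):** IGT is given as "FBG <7.0 mmol/L or 2h PBG ≥7.8 and <11.1 mmol/L".
- **End points (2.6.1):** incident diabetes under the 2017 national guideline is one of the two end-point indexes.
- **Sample size (2.10):** the calculation rests on conversion to diabetes, at 10% a year in control; for the other arm, "We predicted that the annual conversion rate of IGT into T2DM was 5.7% in the TCM comprehensive intervention group".
- **Follow-up (2.7, Discussion, Table 1):** 24 weeks of treatment, then six-monthly visits to 30 months; "follow-up is continued for another two years, which is to observe the short-term and long-term effects of TCPMs". The Table 1 row "Determine withdrawal criteria" is ticked at every visit, including 30 months.
- **Missing data (2.11):** "The last observation carried forward (LOCF) method will be used for the missing data supplement".
- **Adverse events (2.8):** events are "retested in 24 hours, 7 days, and 14 days according to the situation" and tracked until stable.

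No section describes ascertaining diabetes after a suspension exit.

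**The concern.** A rise in glucose is the path to incident diabetes. Removing people from the study because of it makes loss to follow-up depend on the outcome. The decision is also a site judgement, made unblinded, in arms that participants chose for themselves, so the exit rate could differ between arms for reasons other than treatment effect.

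If the exit value is already in the diabetic range, the event can be counted and nothing is lost. The difficulty is the participant whose glucose climbs clearly but stays short of diabetes. That person is at high risk of converting, and the visits that would show it are not made. An analysis plan can decide how to code the exit but cannot supply the missing visits.

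The labelled primary outcome (change in FBG, 2h PBG and HbA1c, section 2.6.2) is not part of this concern.

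**Working it through.** **1. The plan's own figure.** Section 2.10 reports n = 299.94 per group (one-sided α = 0.05, β = 0.1). Annual rates of 10% and 5.7% give 669 per group by the pooled two-proportion formula. Doubling both rates (20% vs 11.4%) gives 305 pooled, or unpooled (1.645 + 1.282)² × (0.2×0.8 + 0.114×0.886) / 0.086² = 302, close to the stated figure. The doubling is an inference, but it suggests that the trial was sized on diabetes accumulated over about two years.

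**2. Can a rise be obvious and still not diabetes?** The 2h PBG entry range is 7.8 to <11.1 mmol/L. A move from 8.0 to 10.5 is (10.5 − 8.0)/8.0 = +31% and is still IGT. The example is hypothetical, but the rule's wording does not exclude it.

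**3. What does *invalid* mean for the end point?** The same sentence gives the same label to severe or frequent hypoglycemia, so the label cannot stand for incident diabetes. Two codings remain for a sub-diabetic exit:

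- scored as diabetes: a case is recorded that never met the section 2.6.1 definition;
- not scored as diabetes: the participant stays a non-case, possibly through LOCF.

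Neither gives the true status.

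**4. Observation lost per exit.** Post-baseline glucose visits in Table 1: weeks 4, 8, 12, 16, 20, 24 and months 12, 18, 24, 30, so 10.

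| Exit at | Months elapsed | Visits lost | Time lost |
|---|---|---|---|
| Week 12 | 2.76 | 7 of 10 | (30 − 2.76)/30 = 91% |
| Week 24 | 5.52 | 4 of 10 | (30 − 5.52)/30 = 82% |

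**5. When cases arise** (annual rates held constant, an assumption).

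- Risk to 2.5 years: control 1 − 0.9^2.5 = 0.2316; TCPM 1 − 0.943^2.5 = 0.1365. Per 300: 69.5 vs 40.9. Difference 9.5 points, ratio 0.59.
- Risk to week 24 (0.46 years): 0.0473 and 0.0266. Share arising later: (0.2316 − 0.0473)/0.2316 and (0.1365 − 0.0266)/0.1365, about 80% in each arm.
- Risk from week 24 to 2.5 years (2.04 years) if still free of diabetes: 1 − 0.9^2.04 = 19.3%; 1 − 0.943^2.04 = 11.3%.

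**6. Illustration A: exits coded as non-cases, the same share f of true cases missed in both arms.** Both risks are multiplied by (1 − f). Power is for a two-proportion z test, 300 per arm, two-sided 0.05 (as in section 2.11), pooled null variance.

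| f (assumed) | Cases, control vs TCPM | Difference (points) | Ratio | Power |
|---|---|---|---|---|
| 0 | 69.5 vs 40.9 | 9.5 | 0.59 | 85% |
| 10% | 62.5 vs 36.8 | 8.6 | 0.59 | 81% |
| 20% | 55.6 vs 32.8 | 7.6 | 0.59 | 75% |
| 30% | 48.6 vs 28.7 | 6.7 | 0.59 | 68% |

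Unequal loss can push either way. With 40% missed in control and 20% in TCPM, the difference is 0.2316×0.6 − 0.1365×0.8 = 3.0 points. With 20% and 40%, it is 0.2316×0.8 − 0.1365×0.6 = 10.3 points.

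**7. Illustration B: exits scored as diabetes, k people per arm who would never convert.** Each risk rises by k/300.

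| k per arm (assumed) | Risks | Difference (points) | Ratio | Power |
|---|---|---|---|---|
| 3 (1%) | 24.2% vs 14.6% | 9.5 | 0.61 | 84% |
| 6 (2%) | 25.2% vs 15.6% | 9.5 | 0.62 | 83% |
| 15 (5%) | 28.2% vs 18.6% | 9.5 | 0.66 | 79% |

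If exits are unequal, the gap between the two codings changes by (control exits − TCPM exits)/300, or 0.33 points per person.

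**The case against.** The strongest reply is that everyone enters with IGT, so a rise marked enough to call for removal may simply mean progression to diabetes. The event would then be counted and nothing lost. The exact cut-off may also sit in the full protocol that this article condenses. Both points are fair, and the missing threshold alone is not the complaint. But the rule as written is not limited to diagnosed diabetes, and the instruction to leave the study is stated text, not an omission.

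Second, the sentence does give a disposition: these people are kept as failures. On that plainest reading, Illustration B applies and the damage is modest; the larger power losses in Illustration A belong to the other reading. That stands as a limit on size. It does not settle the end point, because a treatment failure shared with hypoglycemia exits is not a diabetes diagnosis.

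Third, the rule's reach beyond week 24 is inferred. Table 1 names withdrawal criteria, the title of section 2.4.6, and several neighbouring suspension items concern the study drug. If the rule stops at week 24, only exits in the treatment period matter; but each of those still loses at least the four follow-up visits.

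Finally, it may be defended as a safety rule. Stopping or changing treatment meets that need, and ending follow-up adds no protection. The adverse-event retests at up to 14 days and tracking until stable do not replace visits to 30 months.

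**Conclusion.** The concern holds and should be fixed. The suspension rule ends observation of incident diabetes on a rise in the variable that defines it, and the protocol provides no ascertainment afterwards. What is firm is the loss per exit: 82% to 91% of follow-up time for an exit between weeks 24 and 12. The effect on the comparison is not determinable, because the documents give neither the number of exits nor their split between arms. The difference, ratio and power figures are illustrations that assume constant annual rates, 300 per arm and the loss shares or exit counts shown. Confidence is medium, since the harm depends on how often the rule is applied below the diabetic range.

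**What to change.** Amend section 2.4.5 so that a marked glucose rise stops or changes study treatment but does not end follow-up. Specifically:

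- At that point, classify diabetes by the section 2.6.1 definition.
- Keep the participant on the Table 1 visits to 30 months unless consent is withdrawn.
- Record the name and start date of any glucose-lowering drug in the existing concomitant-medication row, so that later values can be read as on or off such drugs.
- Do the same, where the participant agrees, for those who stop for poor efficacy under section 2.4.6.
- Do not count hypoglycemia exits as diabetes events.

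The cost is small: protocol wording and exit-reason codes on the case report form, since the visits and the medication record are already scheduled to 30 months. The downsides are some visits by people off treatment, an occasional extra glucose test when the exit falls between visits, and later values that rescue drugs may lower, which could hide some conversions.

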#### 2.4.6. Withdrawal Criteria

Participants who privately cease to accept medical treatment or conduct testing or who become impossible to contact are also considered withdrawnParticipants who cannot continue because of poor clinical efficacy, intolerance due to adverse reactions, economic reasons, or moves

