#### 2.12.3. Measures for Compliance of Participants

Researchers should distribute the research drugs to participants in time and supervise the use of drugs. Participants with poor compliance should strengthen the follow-up. Participants are required to bring the remaining drugs distributed last time in order to inspect the drug compliance.(1)$$\begin{array}{c} \text{Drug compliance}=\left[\frac{\left(\text{dispensing}-\text{remaining}\right)}{\text{dispensing}}\right]\times 100\%. \end{array}$$

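### Drug intake outside 80–120% is an exit only the TCPM arm can meet; read naturally as leaving the study, it lets LOCF hide that arm's later diabetes.

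*Protocol article*

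**What the plan says.** All references are to the protocol article.

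- **Suspension rule (2.4.5).** The list includes "poor drug compliance, such as failure to take at least 80% and no more than 120% of the prescribed amount".
- **Who has study drug (2.5).** "The control groups will conduct lifestyle intervention alone"; the Discussion confirms that there is no placebo. Section 2.12.3 computes compliance from drug dispensed and drug returned.
- **Withdrawal (2.4.6).** People who stop treatment or testing on their own, "or who become impossible to contact are also considered" withdrawn.
- **Poor compliers (2.12.3).** "Participants with poor compliance should strengthen the follow-up".
- **Full-analysis set (2.11).** One evaluation after starting drug is enough to be included: "The FAS is the dataset composed of participants who have at least one postmedication evaluation data".
- **Missing data (2.11).** A single method is named, with no end point exempted: "The last observation carried forward (LOCF) method will be used for the missing data supplement".
- **Per-protocol set (2.11).** Compliance is already a condition of entry here: "The PPS is the dataset composed of participants who meet the inclusion criteria, show good compliance, and complete the treatment plan".
- **End points and visits.** Incident diabetes is an end point (2.6.1), and annual conversion to diabetes is the quantity used for the sample size (2.10). Table 1 schedules glucose and HbA1c to month 30 and has a row "Determine withdrawal criteria" ticked at every visit.

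**The concern.** An exit rule tied to study drug in a trial whose control arm has none operates on one side only. If a suspended person leaves, diabetes that develops afterwards is not observed. LOCF then replaces the unobserved period with the last recorded state, which for most people suspended during the 24 drug weeks is diabetes-free. Conversions disappear from the TCPM arm and not from the control arm, even if TCPM does nothing and non-adherers carry no different risk.

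Two features that might seem protective are not:

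- The loss happens after entry, so adjusting for baseline differences between the self-selected groups would not remove it.
- The per-protocol set excludes the same people and cannot serve as a check.

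Section 2.4.5 does score a marked glucose rise at exit as treatment failure. That covers people who are worsening when they leave, not those who convert later.

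**Working it through.** **1. Does suspension mean leaving?** It is not written out for the compliance item.

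- *For:* other entries in the same list concern people unfit or unwilling to continue the study, or withdrawn from it. The word also in section 2.4.6 implies that the preceding list describes withdrawals.
- *Against:* explicit withdrawal wording is attached only to the glucose-rise/hypoglycemia entry. Section 2.12.3 asks for stronger follow-up of poor compliers, and Table 1 makes no exception for people off drug.

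Leaving is the more natural reading. The section 2.12.3 sentence sits among drug-supervision measures and does not say that outcome visits continue after suspension.

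**2. Inputs.**

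- From the article: 10% annual conversion in controls, 5.7% planned for TCPM, 300 per arm (2.10); two-sided 0.05 tests (2.11); last visit at 30 months, i.e. 2.5 years (Table 1).
- Assumed: a fraction *f* of the TCPM arm is suspended at week 12 and leaves; equal risk in non-adherers; no differential control loss; LOCF applied to diabetes status. The article does not give *f*; 5–20% is used.

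**3. Incidence with no true effect.** F(t) = 1 − 0.9^t.

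- F(2.5) = 0.2316, the true 30-month incidence in both arms
- F(12/52) = 0.0240
- F(24/52) = 0.0475

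Observed TCPM incidence = (1 − f)·F(2.5) + f·F(12/52).

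Missed conversions = 300·f·(0.2316 − 0.0240).

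The last column is the chance that a two-proportion z-test rejects in favour of TCPM, by exact binomial enumeration (nominal 2.5%).

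| f | Observed TCPM | Risk ratio | Missed per 300 | False positive favouring TCPM |
|---|---|---|---|---|
| 5% | 0.2212 | 0.955 | 3.1 | 4.9% |
| 10% | 0.2108 | 0.910 | 6.2 | 8.9% |
| 20% | 0.1901 | 0.821 | 12.5 | 23.8% |

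**4. Sensitivity.**

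- *Time of suspension:* for f = 10% and 20%, week 4 gives 0.903 and 0.807; week 24 gives 0.920 and 0.841.
- *Time of assessment, f = 10%:* months 12, 18, 24 and 30 give 0.924, 0.916, 0.913 and 0.910.
- *Assessed at week 24 only, f = 5%, 10%, 20%:* ratios 0.975, 0.951 and 0.901; false-positive chance 2.9%, 3.4% and 4.6%; about 0.4, 0.7 and 1.4 conversions missed per 300.
- *Half of the suspended still assessed to month 30:* ratios 0.978, 0.955 and 0.910; false-positive chance 3.5%, 4.9% and 8.9%. If all are assessed, the ratio is 1.00.
- *Loss in both arms at week 12 (TCPM/control):* 20%/10% gives 0.1901/0.2108 = 0.90; 20%/20% gives 1.00; 10%/20% gives 0.2108/0.1901 = 1.11.

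**5. Planned rates (5.7% vs 10% per year), f = 10%.**

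- Full follow-up: (1 − 0.943^2.5)/0.2316 = 0.1365/0.2316 = 0.589.
- LOCF: TCPM incidence by week 12 is 1 − 0.943^(12/52) = 0.0135, so (0.9 × 0.1365 + 0.1 × 0.0135)/0.2316 = 0.1242/0.2316 = 0.536.
- Full follow-up, suspended people reverting to 10% per year after week 12: their incidence is 1 − 0.943^(12/52) × 0.9^(2.5 − 12/52) = 0.2232, so (0.9 × 0.1365 + 0.1 × 0.2232)/0.2316 = 0.627.

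**6. Normalization of blood glucose (2.6.1).** Assuming it occurs at 10%, 20% or 30% per year and is not reversed, the same formula with f = 10% gives ratios of 0.910, 0.912 and 0.913. For this end point a lower ratio counts against TCPM.

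**The case against.** The strongest reply is that the damaging consequence is inferred. Suspension and withdrawal are separate lists, the compliance item carries no instruction to withdraw, and the one sentence on handling poor compliers asks for more follow-up. A condensed article may leave to the full protocol whether outcome visits continue, and to the analysis plan how LOCF applies to an event end point and when that end point is read. If all suspended people are assessed, the artefact is zero. The suspended share has no source, the effect at week 24 is small, and control exits through reluctance, poor efficacy, loss of contact or moves could cancel or reverse the bias.

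Much of this stands as a limit on size and on confidence. It does not remove the defect. The one-sided exit rule and the unrestricted LOCF statement are both in the text, and nothing in the text secures outcome visits after suspension. If continued follow-up is intended, sections 2.4.5 and 2.12.3 point in different directions and should be reconciled. Relying on unplanned control losses to balance a built-in TCPM loss is not a safeguard, and an analysis plan cannot recover visits that were never made.

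**Conclusion.** The concern holds and should be fixed, with medium confidence because it depends on reading suspension as leaving the study. Under that reading, with LOCF applied to diabetes status, the compliance rule alone would move a null 30-month risk ratio to between 0.96 and 0.82 for 5–20% suspended at week 12. It would raise the false-positive chance favouring TCPM from 2.5% to between 4.9% and 24%; the upper figure needs the top of an assumed range.

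This is one channel of bias on one end point, and the net direction also depends on control losses. No effect is shown on the declared primary outcome, the changes in fasting glucose, two-hour glucose and HbA1c (2.6.2). For normalization of blood glucose the same rule would tend to work against TCPM.

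**What to change.** - In sections 2.4.5 and 2.4.6, state that poor compliance, allergy and drug-related adverse reactions stop study drug only.
- Keep consenting participants on the Table 1 glucose and HbA1c schedule to month 30, and analyse them in the group they entered.
- Use the 80–120% rule only to define the per-protocol set, which already requires good compliance.
- In section 2.12.3, state that strengthened follow-up continues after drug is stopped. This also settles the tension with section 2.4.5.

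The cost is wording, plus already scheduled visits for people who would otherwise have left. The estimated benefit may look smaller: at the planned rates with 10% suspended, the risk ratio moves from 0.54 to 0.59, or to 0.63 if suspended people revert to the control rate. If the full protocol already keeps these people in follow-up, one clarifying sentence is enough.
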